### Variables

The exposure to modifiable risk factors in combination with genomic data (polygenic risk score) in both cases and controls will be expressed as odds ratios (95% CI). Multiple logistic regression models will be built to adjust and determine the strength of association between demographic variables (sex, age, race), traditional risk factors (smoking, diabetes, hypertension, obesity, anxiety and depression, unhealthy diet, physical inactivity, alcohol consumption, and apolipoprotein B/A1 ratio [ApoB/ApoA1], and genetic data [PRS]. For each variable with a higher chance of CVD (significant OR), attributable risk estimate will be calculated for the genetic component (PRS) and other covariables. Fig 2 shows the Polygenic Risk Score flowchart.

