## Abstract

Atherosclerotic Cardiovascular Disease (ASCVD) represents the leading cause of death worldwide, and individual screening should be based on behavioral, metabolic, and genetic profile derived from data collected in large population-based studies. Due to the polygenic nature of ASCVD, we aimed to assess the association of genomics with ASCVD risk and its impact on the occurrence of acute myocardial infarction, stroke, or peripheral artery thrombotic-ischemic events at population level. CardioVascular Genes (CV-GENES) is a nationwide, multicenter, 1:1 case-control study of 3,734 patients in Brazil. Inclusion criterion for cases is the first occurrence of one of the ASCVD events. Individuals without known ASCVD will be eligible as controls. A core lab will perform the genetic analyses through low-pass whole genome sequencing and whole exome sequencing. In order to estimate the independent association between genetic polymorphisms and ASCVD, a polygenic risk score (PRS) will be built through a hybrid approach including effect size of each Single Nucleotide Polymorphism (SNP), number of effect alleles observed, sample ploidy, total number of SNPs included in the PRS, and number of non-missing SNPs in the sample. In addition, the presence of pathogenic or likely pathogenic variants will be screened in 8 genes (*ABCG5*, *ABCG8*, *APOB*, *APOE*, *LDLR*, *LDLRAP1*, *LIPA*, *PCSK9*) associated with atherosclerosis. Multiple logistic regression will be applied to estimate adjusted odds ratios (OR) and 95% confidence intervals (CI), and population attributable risks will be calculated.

**Clinical trial registration:** This study is registered in clinicaltrials.gov (NCT05515653).

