From a public health system perspective, epidemiological features of cardiovascular health in developing countries have been described [16, 17], but there is still an urgent need for studies with geographic representation to allow both regional and ethnic diversity as essential elements to data acquisition and analysis of CVD risk. We designed the case-control study CardioVascular-Genes (CV-GENES) to determine the population attributable fraction estimates of genetic profile in the occurrence of acute myocardial infarction, stroke, or peripheral artery thrombotic-ischemic events, after adjustment for potentially modifiable CVD risk factors in Brazil [18, 19].

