### Data analysis

#### Quantitative variables and statistical analysis

The Hardy-Weinberg genetic equilibrium test will be evaluated in the control group using the chi-square test or Fisher’s exact test. To estimate the association between genetic polymorphisms and risk of CVD, univariate and multiple unconditional logistic regression analyses will be conducted [32–36].

Initially, univariate binary logistic regression analyses will be performed. Thus, covariates with a p-value < 0.20 in univariate regression analyses will be considered in multiple logistic regression analysis with selection of variables according to the backward elimination technique [37, 38]. The selection process in the backward elimination allows the sample size to adjust and always uses the maximum available sample as the number of variables in the model drops [37]. Occasionally, covariates judged as confounding factors by the investigator may be forced into the final backward regression model.

Additional multiple logistic regression analyses may also be conducted using a variant of the Purposeful Selection algorithm described by Bursac *et al*. [38].

The assumption of linearity on the logit scale (log-odds) between each quantitative covariate and the binary response variable in binary logistic regression analysis will be evaluated with the construction of “Smoothed Scatter Plots” and the method of fractional polynomials [35–39]. When the assumption is not satisfied, quantitative covariates will be categorized for use in logistic regression using cut-off points, according to the literature, distribution tertiles or optimal cut-off obtained from the Receiver Operating Characteristic (ROC) curve, whichever is deemed most appropriate. In case of an optimal cut-off point, it will be defined as the one that maximizes the Youden index [39, 40].

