#### Estimation of population attributable risk

To characterize the study population, categorical variables will be described as counts and proportions and compared with Pearson’s chi-square test or with Fisher’s exact test [41]. Normally and asymmetrically distributed quantitative variables will be expressed as mean (standard deviation) or median (interquartile range), respectively [42]. Normality will be assessed by visually inspecting histograms and applying normality tests, if appropriate [43, 44]. Comparison of these continuous type variables will be carried out with Student’s t test for independent samples or Mann-Whitney test for non-parametric distribution [41].

All statistical analyses will follow the complete case analysis principle. All hypothesis tests will be 2-sided and p-value<0.05 considered statistically significant. Statistical data analysis will be conducted with SAS 9.4 (SAS Institute, Cary, NC).

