## Discussion

We have designed and launched a nationwide multicenter observational case-control study to determine the population attributable fraction estimate of genetics in the overall risk of first occurrence of ASCVD. We will be able to assess the polygenic risk score and ASCVD and also a set of specific monogenic inheritance genes associated with atherosclerosis at the population level. This national effort will provide clinical and genetic data to support the National Program in Genomics and Precision Medicine (GENOMAS BR), which currently aims to screen 100,000 Brazilians.

AMI worldwide is associated with nine modifiable risk factors (ApoB/ApoA1 ratio, hypertension, diabetes, abdominal obesity, smoking, psychosocial factors, poor diet, regular alcohol consumption and lack of regular physical activity). Beyond these nine above-mentioned risk factors, one additional factor, cardiac risk, is also associated with stroke. These factors account for 90% of the population attributable risk (PAR) of both acute myocardial infarction and stroke. Therefore, it is biologically plausible that the genetic background might also play a role in the remaining 10% of PAR of ASCVD.

In this study, the contribution of the genetic background in the risk of ASCVD among Brazilian individuals will be ascertained by the analysis of variants with a potential direct effect of disease manifestation (monogenic diseases). The polymorphisms will be ascertained in genes that compound the risk in association to each other (polygenic diseases), which behave as factors of susceptibility to a disease, in the “two hits” pathogenic model, where there is a direct interaction of a genetic background with environmental factors for the development of the disease [8–10].

A previous study of 8,795 individuals of European, South Asian, Arab, Iranian, and Nepalese origin from the INTERHEART case-control study performed a genotyping of 1,536 SNPs from 103 genes evaluated as well as analyzed previous established cardiovascular risk factors. Thirteen polymorphisms were associated with increased cardiovascular risk, 11 of which were related to serum levels of APOB/A1 ratio, 1 associated to LDL-cholesterol receptor and 1 to Apolipoprotein E [7].

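### The genetic attributable risk, the study's stated aim, is to be calculated only if the odds ratio is significant; it should be reported with its interval whatever the p-value

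*Protocol article*

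**What the plan says.** The Introduction gives the aim as "to determine the population attributable fraction estimates of genetic profile in the occurrence of acute myocardial infarction, stroke, or peripheral artery thrombotic-ischemic events", and the Discussion repeats it as "to determine the population attributable fraction estimate of genetics in the overall risk of first occurrence of ASCVD". The Abstract says without qualification that "population attributable risks will be calculated".

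The rule in the Variables section is narrower: "For each variable with a higher chance of CVD (significant OR), attributable risk estimate will be calculated", and the sentence applies this to the PRS as well as to the other covariables. Significance is defined under Estimation of population attributable risk: "All hypothesis tests will be 2-sided and p-value<0.05 considered statistically significant". Despite its heading, that section covers only descriptive statistics, complete-case analysis and software, so it does not lift the condition.

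The section on quantitative variables and statistical analysis adds a selection step: "covariates with a p-value < 0.20 in univariate regression analyses will be considered in multiple logistic regression analysis with selection of variables", by backward elimination. The one exemption is optional and covers covariates that the investigator regards as confounders. Nothing says that the PRS stays in the model.

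**The concern.** The quantity that the study exists to estimate is made conditional on its own significance test. This has two consequences. If the PRS odds ratio is not significant, no attributable fraction is produced, although a small value with a tight interval would be a useful result. If it is significant, the reported value comes from a distribution with its lower part cut off, so on average it exceeds the truth. The weaker the true effect, the larger the excess, so a weak factor would be overstated more than a strong one when their attributable risks are set side by side.

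The selection step can act as a second filter, because the exposure of interest is not protected from it. The Abstract and the Variables section also disagree on whether the condition exists.

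**Working it through.** **Inputs from the article.** Sample size calculation: odds ratio 1.3, allele frequency 10%, dominant model, disease prevalence 10%, power 90%, two-sided α 0.05, 1,867 cases and 1,867 controls. Threshold for a significant odds ratio: two-sided 0.05.

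**Assumptions.** The article gives no attributable-risk formula, so PAR = p_case × (1 − 1/OR) is assumed. The exposure is the single dominant carrier state of the sample size calculation, standing in for the PRS. There is no covariate adjustment and no variable selection.

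**Step 1: reproduce the sample size.**
- Carrier frequency = 1 − 0.9² = 0.19.
- Baseline odds b solve 0.81·b/(1+b) + 0.19·1.3b/(1+1.3b) = 0.10. This gives a risk of 0.0952 in non-carriers and 0.1204 in carriers.
- Carriers among cases: 0.19 × 0.12035/0.10 = 0.2287. Among controls: 0.19 × (1 − 0.12035)/0.90 = 0.1857.
- With H(p) = p ln p + (1−p) ln(1−p) and p̄ the mean of the two frequencies, the likelihood-ratio noncentrality per case-control pair is λ = 2[H(0.2287) + H(0.1857) − 2H(p̄)].
- n = (1.960 + 1.282)²/λ = 1,866.7, so 1,867. The stated figure reproduces. A pooled two-proportion formula gives 1,868, and its power at 1,867 is 0.900.

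**Step 2: true PAR at the design effect.** 0.2287 × (1 − 1/1.3) = 0.0528, or 5.3%.

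**Step 3: where the condition bites.** The standard error of the log odds ratio is √{(1/1,867)[1/(0.2287×0.7713) + 1/(0.1857×0.8143)]} ≈ 0.081. Significance needs a log odds ratio of about 1.96 × 0.081 = 0.159, an observed odds ratio near 1.17. With about 21% carriers among cases, this is a PAR near 0.21 × (1 − 1/1.17) ≈ 3.1%. Over all simulated studies, the smallest PAR that passed was about 2.9%.

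**Step 4: simulation.** 400,000 studies per odds ratio, 1,867 per group, prevalence held at 10%. A PAR counts as calculated if the Wald test is significant with an odds ratio above 1.

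| True OR | True PAR | Not calculated | Mean, all studies | Mean when calculated | Relative excess |
|---|---|---|---|---|---|
| 1.1 | 1.85% | 79% | 1.84% | 4.00% | +116% |
| 1.2 | 3.61% | 39% | 3.59% | 4.60% | +28% |
| 1.25 | 4.45% | 22% | 4.44% | 5.04% | +13% |
| 1.3 (design) | 5.28% | 10% | 5.26% | 5.57% | +6% |
| 1.4 | 6.87% | 1.3% | 6.86% | 6.91% | +0.6% |
| 1.5 | 8.39% | 0.1% | 8.38% | 8.38% | none |

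Without the condition the estimate is essentially unbiased at every odds ratio. Holding the control frequency at 18.57% instead changes little: at 1.1, a true 1.82% averages 3.96% and is calculated in 21% of studies; at 1.2, a true 3.58% averages 4.58% and is calculated in 60%.

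**The case against.** The strongest reply is that the article's own effect sizes are mostly not weak. It designs for 1.3, where the excess is about 0.3 percentage points against a standard deviation of about 1.6. For non-modifiable factors the Discussion cites a Latin American PAR of 0.12 (95% CI 0.02 to 0.42) and speaks of genetics within a remaining 10%. In the same model a true PAR of 12% (odds ratio about 1.73) is always calculated and averages 12.0%; a true 10% (about 1.60) is calculated in more than 99.9% of studies without inflation. This stands. Only toward the lower limit of the cited interval does the rule do real damage: a true 2% is calculated in 24% of studies and averages 4.0%.

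A reader might therefore infer more than the article supports:
- **That the genetic figure must be either absent or materially inflated, or that every published PAR is distorted.** It need not be. Strong factors pass the test almost surely, and conditioning then changes nothing.
- **That a non-significant PRS leaves the aim with no answer.** The Variables section first says that exposures, the PRS included, will be expressed as odds ratios with 95% CI, with no significance condition. What is lost is the attributable fraction itself.
- **That the percentages above describe the PRS.** They describe one unadjusted carrier state. The PRS combines many variants, and its PAR depends on how the score is cut.
- **That the lack of a PAR formula is a fault.** An article may leave that to the full protocol.

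It can also be said that the selection paragraph speaks of covariates and never names the PRS. However, the Variables section groups the PRS with the other covariables, so protection cannot be assumed. A PRS that was eliminated would usually be non-significant anyway, so this adds little to the main point. Finally, the sentence in the Variables section is loosely worded and might be meant to give the PRS a PAR always. If so, it still needs correcting, because the conditional reading is the natural one.

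**Conclusion.** The point holds as a should-fix. The article states a rule that makes its main quantity conditional on significance, and that rule conflicts with the unconditional statement in its Abstract. At the design effect the cost is modest: about a 1 in 10 chance of no genetic PAR, and about 6% relative overstatement otherwise. It becomes serious for odds ratios of about 1.1 to 1.2 and negligible from about 1.4. In the model used, a PAR below about 2.9% could practically not be reported.

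These sizes rest on an unadjusted binary exposure, an assumed PAR formula and no modelling of variable selection, so they are illustrative. The defect of principle does not depend on them: if the effect is strong the condition serves no purpose, and if it is weak the condition suppresses or inflates the answer.

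**What to change.** - Delete the significance condition from the attributable-risk sentence in the Variables section, so that it agrees with the Abstract.
- State that the PRS is kept in every model and is exempt from the p<0.20 screen and from backward elimination.
- Report the PAR with 95% CI for the PRS and for each risk factor listed in the Variables section, whatever the p-value. Each such factor then needs an adjusted odds ratio from a model that contains it.

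The cost is wording only; the sample size of 1,867 per group and the data collection are unaffected. Some reported intervals will include zero. The change should be made before the data are analysed, since afterwards the choice would depend on the results.

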**Fig 2 pone.0289439.g002:**
[figure not shown]
Polygenic risk score flowchart.

Table 1 displays the biochemical tests and respective stability and methodology. All biochemical and genetic tests will be run at the same centralized core lab.

**Table 1 pone.0289439.t001:** Biochemical tests and respective stability and methodology.

Test description	Refrigerated Stability	Frozen Stability	Methodology
Glycosilated hemoglobin, whole blood	(2–8 °C): 7 days;	(-20 °C): 30 days;	Ion exchange Column chromatography in HPLC system
Apolipoprotein A-1, serum	(2–8 °C): 8 days;	(-20 °C): 2 months;	Immunoturbidimetric
Apolipoprotein B, serum	(2–8 °C): 8 days;	(-20 °C): 2 months;	Immunoturbidimetric
Cholesterol, serum	(2–8 °C): 7 days;	(-20 °C): 3 months;	Colorimetric enzyme
HDL Cholesterol, serum	(2–8 °C): 7 days;	(-20 °C): 3 months;	Colorimetric enzyme
Cholesterol, LDL Fraction, serum	(2–8 °C): 7 days;	(-20 °C): 3 months;	Calculation based on Friedewald formula
Cholesterol, VLDL Fraction, serum	(2–8 °C): 7 days;	(-20 °C): 3 months;	Martin and colleagues’ formula
Triglycerides, serum	(2–8 °C): 7 days;	(-20 °C): 1 year;	Colorimetric enzyme
Creatinine, serum	(2–8 °C): 5 days;	(-20 °C): 1 year.	Colorimetric kinetic
Sodium, serum	(2–8 °C): 7 days;	(-20 °C): 6 months;	Potentiometric
Potassium, serum	(2–8 °C): 7 days;	(-20 °C): 6 months;	Potentiometric
Sodium, spot, urine	(2–8 °C): 7 days;	(-20 °C): 6 months;	Potentiometric
Potassium, urine	(2–8 °C): 7 days;	(-20 °C): 3 months;	Potentiometric
Creatinine, spot, urine	(2–8 °C): 5 days;	(-20 °C): 1 year;	Colorimetric kinetic
Albuminuria, spot, urine	(2–8 °C): 14 days;	(-20 °C): 6 months;	Immunoturbidimetric assay

### Data source and measurement

Data will be collected through electronic case report forms (eCRFs) specifically designed for this study by using the REDCap software [24]. Demographic variables, prior and inpatient use of medications, biochemical tests (glycosilated hemoglobin, serum apolipoprotein A1, serum apolipoprotein B, total serum cholesterol and fractions [HDL-c, LDL-c, and VLDL-c], serum triglycerides, serum sodium, serum potassium, and measurement of sodium, potassium, creatinine, and albumin in a spot urine sample), and the genetic data (PRS) will be collected.

For the preparation of the whole exome sequencing and low pass whole genome sequencing, the paired-ends libraries will be prepared using 50 ng of DNA as input and library preparation enzymatic fragmentation (EF) Kit 2.0 (Twist Bioscience) with combinatorial dual indexes (Twist Bioscience) reagent kit, following the manufacturer’s instructions. Library preparation for WES will include a hybridization capture step with Twist Exome 2.0 probes (Twist Bioscience), following the manufacturer’s instructions. Exome and low pass genome will be sequenced on a NovaSeq 6000 platform (IlIumina) using S4 flow cell with 300 cycles (2 x 150 bp—paired end). Run data and quality control will be monitored in NovaSeq control software. For the preparation of the whole exome sequencing and low pass whole genome sequencing, the paired-ends libraries will be prepared using 50 ng of DNA as inputs and enzymatic fragmentation and combinatorial dual indexes (Twist Bioscience) reagent kit, following the manufacturer’s instructions. Exome and low pass genome will be sequenced on a NovaSeq 6000 platform (IlIumina) using S4 flow cell with 300 cycles (2 x 150 bp—paired end). Run data and quality control will be monitored in NovaSeq control software.

The genetic evaluation will be performed through the association of low-pass whole genome sequencing (WGS) (coverage 0.5-1x) with data imputation and whole exome sequencing (WES) (average coverage 90x). The method of PRS calculation is described in the S3 File [25–27]. In addition, the presence of pathogenic or likely pathogenic variants will be screened in 8 genes (*ABCG5*, *ABCG8*, *APOB*, *APOE*, *LDLR*, *LDLRAP1*, *LIPA*, *PCSK9*) associated with atherosclerosis, from the WES (S3 File) [28–30]. For patients in whom novel monogenic variants are identified, those variants will be classified for their pathogenicity according to The American College of Medical Genetics and Genomics (ACMG) criteria [31]. For the Polygenic Risk Score calculation, only Single Nucleotide Polymorphisms previously associated with an increased cardiovascular risk will be selected.

Both protocols (WGS and WES) were validated previously to this study by using standard control and samples with known results (orthogonal tests) and the data were compared. In addition, coverage, Polymerase Chain Reaction duplicates and other parameters were evaluated.

### Data analysis

#### Quantitative variables and statistical analysis

The Hardy-Weinberg genetic equilibrium test will be evaluated in the control group using the chi-square test or Fisher’s exact test. To estimate the association between genetic polymorphisms and risk of CVD, univariate and multiple unconditional logistic regression analyses will be conducted [32–36].

Initially, univariate binary logistic regression analyses will be performed. Thus, covariates with a p-value < 0.20 in univariate regression analyses will be considered in multiple logistic regression analysis with selection of variables according to the backward elimination technique [37, 38]. The selection process in the backward elimination allows the sample size to adjust and always uses the maximum available sample as the number of variables in the model drops [37]. Occasionally, covariates judged as confounding factors by the investigator may be forced into the final backward regression model.

Additional multiple logistic regression analyses may also be conducted using a variant of the Purposeful Selection algorithm described by Bursac *et al*. [38].

The assumption of linearity on the logit scale (log-odds) between each quantitative covariate and the binary response variable in binary logistic regression analysis will be evaluated with the construction of “Smoothed Scatter Plots” and the method of fractional polynomials [35–39]. When the assumption is not satisfied, quantitative covariates will be categorized for use in logistic regression using cut-off points, according to the literature, distribution tertiles or optimal cut-off obtained from the Receiver Operating Characteristic (ROC) curve, whichever is deemed most appropriate. In case of an optimal cut-off point, it will be defined as the one that maximizes the Youden index [39, 40].

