### Eligibility criteria

Cases: All participants aged ≥18 years who are hospitalized due to the first occurrence of an acute myocardial infarction (AMI), stroke, or peripheral artery thrombotic event, presenting in the first 7 days from symptom onset will be screened (S3 File).

Eligible cases must have signs and/or symptoms compatible with the acute manifestation of ASCVD. Case definitions include diagnostic criteria based on national and international guidelines. Acute myocardial infarction is defined as: clinical presentation, electrocardiogram patterns (new pathological Q waves, and/or ST-segment elevation of 1 mm in ≥ 2 contiguous leads, or 2 mm from V1 to V3, or new left bundle branch block, or new changes in the ST-T segment, and cTnI or cTnT curve compatible with acute myocardial injury of ischemic nature (which is currently named a type 1 acute MI). Stroke is defined as clinical signs of rapid development of focal or global brain function disorder, lasting more than 24 hours, with no apparent cause other than that of vascular origin (does not include trauma, cancer, infection of the central nervous system), and Computed Tomography or Magnetic Ressonance Imaging with positive results. Peripheral artery thrombotic event is defined as clinical presentation (pain, burning sensation, absence of pulse, decreased local temperature, changes in color) and diagnostic tests (Doppler ultrasound, angiotomography, or arteriography) that show interruption of flow to the lower limbs acutely, of embolic or thrombotic cause, leading to distal ischemia [20–23].

Controls: All participants aged ≥18 years seeking medical care for non-ASCVD conditions will be screened and enrolled during hospitalization; and healthy individuals with no clinical complain will also be screened and enrolled at the same community. Cases and controls will be recruited in a 1:1 ratio adjusted for sex and age.

Exclusion criteria for both cases and controls are previously known ASCVD, e.g., chronic coronary artery disease, stable angina, previous myocardial infarction, percutaneous revascularization procedures (coronary, cerebrovascular, or peripheral), surgical revascularization procedures in any arterial vascular bed, transient ischemic attack, stroke, aortic aneurysm, intermittent claudication, peripheral artery disease that led to amputation.

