### Sample size calculation

We applied the following statistical assumptions: odds ratio for genetics was set at 1.3, allele frequency of 10%, inheritance model was dominant (since the presence of only one polymorphic allele is required to the risk calculation), the prevalence of CVD in the general population of 10%, statistical power of 90%, type I error rate (α) of 0.05, 2-sided significance tests, resulting in a sample of 1,867 cases and 1,867 controls. Sample size calculation was performed using Quanto Software Version 1.2.4.

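### Sex and age are balanced by recruitment, yet nothing protects them from the p < 0.20 screen and backward elimination, so odds ratios of age- or sex-related risk factors can be modestly biased

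*Protocol article*

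**What the plan says.** On recruitment, the Eligibility criteria section states: "Cases and controls will be recruited in a 1:1 ratio adjusted for sex and age". It gives no matching tolerance and does not say whether matching is by pair or by frequency.

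On analysis, the section on quantitative variables and statistical analysis states that "univariate and multiple unconditional logistic regression analyses will be conducted". Entry to the multiple model is decided by a univariate test: "covariates with a p-value < 0.20 in univariate regression analyses will be considered in multiple logistic regression analysis with selection of variables" by backward elimination. The only safeguard is: "Occasionally, covariates judged as confounding factors by the investigator may be forced into the final backward regression model". Sex and age are not named there.

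The Variables section does list them: "Multiple logistic regression models will be built to adjust and determine the strength of association between demographic variables (sex, age, race" and the traditional risk factors and polygenic risk score (PRS) follow. For variables with a significant odds ratio (OR), an "attributable risk estimate will be calculated for the genetic component (PRS) and other covariables".

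**The concern.** Recruiting controls to resemble cases on sex and age removes, by design, the marginal association of those factors with case status. It does not remove the need to adjust for them: an unconditional analysis of matched or balanced data must keep the balancing factors in the model. A univariate p-value is therefore the wrong test for exactly these two variables. A large p-value says that recruitment worked, not that adjustment is unnecessary.

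If the rule is followed and both are dropped, the ORs of risk factors that vary with age or sex move toward 1, and so do the attributable risks built on them. The study sets the genetic contribution against these figures. Separately, the Variables section plans to estimate associations for sex and age themselves. After balancing, such estimates reflect how controls were recruited and not risk.

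**Working it through.** **1. The plan's own figure.** Sample size calculation: "odds ratio for genetics was set at 1.3, allele frequency of 10%, inheritance model was dominant", with disease prevalence 10%, power 90% and two-sided α 0.05.
- Carrier frequency = 1 − 0.9² = 0.19.
- Solving for the baseline risk that gives 10% prevalence yields carrier frequencies of 0.2287 in cases and 0.1857 in controls.
- The unmatched 1:1 likelihood-ratio formula gives 1,866.7 per group, against 1,867 stated. The figure reproduces; a matched-pair variant gives 1,869.

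**2. Can sex and age pass the screen?** Simulation with 1,867 per group and 200 to 300 replicates per scenario. Assumed, because the article gives no values: case age mean 60, SD 11; 65% male.

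| How controls resemble cases | Age passes p < 0.20 | Sex passes | Both dropped |
|---|---|---|---|
| Exact, ±5-year pairs, or 10-year bands (sex exact) | 0% | 0% | 100% |
| Same expected distribution only | 19% | 17% | 68% |
| Controls 2 years younger on average, 62% male | 100% | 73% | 0% |

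Arithmetic for ±5-year pairs explains the zero:
- Control age variance is 121 + 100/12 = 129.3, so the unpaired standard error of the mean age difference is √((121 + 129.3)/1,867) = 0.366 years.
- Passing p < 0.20 needs a difference of about 1.28 × 0.366 = 0.47 years.
- Under symmetric matching the difference has SD (10/√12)/√1,867 = 0.067 years, so 0.47 is about 7 SDs away.
- A systematic shift of 0.5 years is enough to change this: age then passed in 64% of runs. For age, the drop rate thus depends on fine detail of the control pool.

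**3. Effect of omitting them when balance holds.** A binary risk factor (prevalence about 0.30) was related to age and sex with assumed strengths, under ±5-year matching. PAR = P(exposed | case) × (1 − 1/OR).

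| True OR | Factor–age OR per 10 years | Factor–sex OR | OR without / with sex and age | PAR without / with |
|---|---|---|---|---|
| 2.0 | 1.3 | 1 | 1.96 / 1.98 | 0.225 / 0.228 |
| 2.0 | 1.6 | 1 | 1.92 / 2.00 | 0.221 / 0.231 |
| 2.0 | 2.0 | 1 | 1.85 / 1.99 | 0.213 / 0.232 |
| 3.0 | 1.0 | 2 | 2.93 / 3.01 | 0.369 / 0.374 |
| 3.0 | 1.6 | 2 | 2.74 / 2.99 | 0.354 / 0.371 |
| 3.0 | 2.0 | 2 | 2.59 / 2.98 | 0.340 / 0.368 |
| 1.3 (unrelated to age and sex) | 1.0 | 1 | 1.304 / 1.304 | 0.055 / 0.055 |

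With a factor–age OR of 2.0 per 10 years, age was significant (p < 0.05) in the joint model in every replicate, although it never passed the univariate screen. The screen removes a covariate that the model needs.

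**4. Large-sample check.** Five age bands balanced 1:1, exposure in controls 10/25/40/55/65%, case shares 10/20/25/25/20% (assumed). Within a band, case exposure = p·OR/(1 − p + p·OR).
- Collapsed control exposure: 0.4275, odds 0.747.
- OR 2.0: case exposure 0.576, odds 1.359; crude OR = 1.359/0.747 = 1.82. PAR 0.576 × (1 − 1/2) = 0.288 falls to 0.576 × (1 − 1/1.82) = 0.259.
- OR 3.0: case exposure 0.658, odds 1.921; crude OR = 1.921/0.747 = 2.57. PAR 0.438 falls to 0.402.

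**5. When balance is imperfect.** In the scenario with controls 2 years younger (true OR 2.0, factor–age OR 1.6), omitting both factors gave 2.10 against 2.00 with them: bias upward.

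**The case against.** The article does not prescribe omission. It lists sex and age among the variables of the adjusting models, Bias control repeats that multivariable models will be used, and confounders may be forced in. The full protocol may settle the point. That softens the concern but does not remove it: the listing shows intent, whereas the selection rule is specific enough to be carried out as written and permits removing them.

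The stated aim is the attributable fraction of the genetic profile. A reader might infer that the main PRS result is compromised. The documents do not support that: a score independent of age and sex is not biased by leaving them out (1.304 in both models).

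A reader might also infer severe attenuation. With exposure rising from 3% to 85% across five equal age bands, 2.0 becomes 1.50 and 3.0 becomes 1.89. The article gives no age gradient for any risk factor, and this one is extreme.

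Nor is bias toward the null guaranteed. It presumes that balance is achieved, and the article's wording on balance is loose. With a 2-year age gap, age passes the screen every time, though backward elimination could still remove it.

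Finally, one might conclude that all p-value selection should give way to a full model. That is a separate and debatable matter. The article defends elimination as using the largest available sample, and under its complete-case rule a fixed full model loses anyone missing any term.

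**Conclusion.** The point stands as a should-fix. The recruitment rule and the selection rule conflict: the second can discard the factors that the first balances. When balance holds, sex is almost always screened out; age is dropped at a rate that depends on how tight and symmetric the matching is. The consequence is confined to risk factors associated with age or sex. Their ORs are low by roughly 1 to 14% (2.0 to about 1.8–1.96; 3.0 to about 2.6–2.9), and attributable risks are lower by up to about 0.03 to 0.04. These sizes rest on assumed age and sex associations, exposure prevalence and case mix; the direction rests on balance being achieved. It is about nil for a PRS independent of age and sex.

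ORs or attributable risks reported for sex and age themselves would describe recruitment, whatever the selection rule does.

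**What to change.** In the section on quantitative variables and statistical analysis, add that sex and age are retained in every multiple model regardless of their univariate or backward-elimination p-value. If controls turn out to be individually matched, conditional logistic regression is the alternative. This is right whether balance is tight or loose: in the simulations, models with both factors recovered the true OR in either case (1.98 to 2.01 for 2.0).

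In the Variables section, add that ORs and attributable risks for sex and age are not interpreted because recruitment fixes their distribution.

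The cost is two sentences. Data collection and the 1,867 per group are unchanged, and two extra terms cost almost no precision at this size. The rest of the selection procedure can stay as it is.
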